Given the positive effects of these two separate but complementary areas of work it is probable that a combination of exercise and SCT-based behaviour change approaches could further improve and maintain health outcomes for people with MS. Step it Up will compare the effect of an exercise plus SCT-based behaviour change intervention with an exercise plus control education intervention on walking mobility among people with MS. Our hypothesis is that those in the exercise and SCT-based intervention will achieve significantly more improvement in walking mobility than the control group post-intervention (12 weeks) and that this improvement will be maintained at 24- and 36- week follow up.

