## Methods/design

### Study design

This will be a multi-centre, double blind, randomised, controlled trial comparing an exercise plus SCT-based intervention with an exercise plus contact control education intervention. Outcomes measures will be administered at weeks 1, 12, 24 and 36. The study will be performed in agreement with the Declaration of Helsinki and is approved by the Health Service Executive Mid-West Research Ethics Committee, the Galway University Hospitals Clinical Research Ethics Committee and the University of Limerick, Faculty of Education and Health Sciences Research Ethics Committee.

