### Sample size

It is assumed that the effect of the intervention yields an average improvement in 6 Minute Walk Test (6MWT) distance of 36 m with an estimated standard deviation of 48.2 m [26]. In order to have 80% power (at the 5% significance level) to detect such a difference in mean improvement in 6MWT over the study period between groups, a sample of size 62 randomised equally to two arms (i.e. 31 per arm) is needed. In order to account for potential drop out a sample of size 72 will be recruited.

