#### Statistical analysis

Suitable numerical statistics and graphical summaries will be used to describe characteristics of the sample at baseline and to assess the validity of any distributional assumptions needed for the formal analysis. The flow of trial participants and the level of missing data for all outcomes will be documented and an analysis into the cause of missingness (if present) will be conducted. All losses to follow-up and dropouts will be accounted, and where possible, reasons documented. The primary analysis will compare differences in the primary response variable, namely the difference in mean steps between the two treatment arms across the 12 week time period. Several analyses will be performed to compare the change in the primary response variable across time and between groups while adjusting for baseline as appropriate. These will include linear mixed models for a continuous response with different covariance structures compared in order to best model the correlation structure within subjects across time. All tests of significance will be two-sided and conducted at an alpha = 0.05 level of statistical significance. A further analysis will be performed to compare the estimated effect of the intervention when imputing values for all missing data in order to investigate the assumptions relating to missingness, and the effect, if any, on the overall conclusion. Multiple imputation will be performed using a Predictive Model Based Method using chained equations where each missing value is replaced by 20 imputed values. The results of each ‘complete’ model (i.e. with imputed values) will be averaged using the Barnard-Rubin adjustment method.

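### The mixed model's covariance structure is to be picked by comparing several on the trial data; if spread grows over follow-up, this mildly distorts the week-36 test, and a pre-specified unstructured covariance avoids it at small cost

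*Protocol article*

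**What the plan says.** All points are from the protocol article.

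- **Statistical analysis.** The primary comparison is "between the two treatment arms across the 12 week time period". The section then states: "Several analyses will be performed to compare the change in the primary response variable across time and between groups". These analyses include linear mixed models "with different covariance structures compared in order to best model the correlation structure within subjects across time". Testing is governed by one rule: "All tests of significance will be two-sided and conducted at an alpha = 0.05 level of statistical significance".
- **Study design.** "Outcomes measures will be administered at weeks 1, 12, 24 and 36". That is one baseline and three follow-up visits.
- **Background.** The hypothesis covers benefit at week 12 and also that "this improvement will be maintained at 24- and 36- week follow up".
- **Sample size.** The calculation assumes an improvement in 6-minute walk "distance of 36 m with an estimated standard deviation of 48.2 m", needs 31 per arm (62), and recruits 72. No other SD and no between-visit correlation is given.

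**The concern.** Compound symmetry and AR(1), the usual simple candidates, assume one variance for all visits. If participants diverge as follow-up lengthens, the true variance is smaller at week 12 and larger at week 36 than the pooled value. The model's standard error is then too large at week 12 and too small at week 36. With 62 to 72 participants, a moderate change in variance is hard to detect, so a fit criterion can prefer the simple structure even though it is wrong. The reported p-value also takes no account of the selection step.

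At stake are a little power at week 12 and some excess false positives in the week-36 test, which carries the maintenance claim. With only three or four fixed visits, selection is not needed.

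**Working it through.** **1. The plan's own figure.** The normal formula is n per arm = 2(z₀.₉₇₅ + z₀.₈₀)² × SD² / difference² = 2 × (1.96 + 0.8416)² × 48.2² / 36² = 28.1, so 29. The t-test version gives 30 per arm (60 in total), against 62 stated, so the figure reproduces. Power at 31 per arm is 83.7% (normal) or 82.5% (t). The 72 recruited allows for 10/72 = 13.9% dropout.

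**2. What pooling the variance does.** Assume, since the documents do not say, that SDs at weeks 12, 24 and 36 are in the ratio 1 : 1.1 : 1.2.

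- Pooled SD = √[(1 + 1.21 + 1.44)/3] = 1.103.
- Standard error ratio, model to truth: 1.103/1 = 1.10 at week 12 and 1.103/1.2 = 0.92 at week 36.
- Type I error = 2[1 − Φ(1.96 × ratio)]: 3.1% at week 12 and 7.2% at week 36.

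For 1 : 1.25 : 1.5 the pooled SD is √[(1 + 1.5625 + 2.25)/3] = 1.267. The ratios are 1.27 and 0.84, and the errors are 1.3% and 9.8%. This is the result if an equal-variance structure is always used. Only ratios matter, so the result does not depend on the outcome's units.

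**3. What selection does.** Null simulations with dropout: 4,000 trials per scenario, 72 participants, three follow-ups, and baseline-adjusted REML. Structures were compound symmetry, AR(1), heterogeneous compound symmetry and unstructured, chosen by AIC. Correlations were 0.7 between adjacent visits and 0.5 between weeks 12 and 36 (0.6 throughout in the equal-SD case). Dropout was either 14% by week 36, or 50% by week 24 and 55% by week 36; the heavier level follows the 50% loss that the Background reports for an earlier exercise trial. Monte Carlo standard error is about 0.35 points. Ranges run across the two dropout levels.

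| SD pattern | Method | Week 12, z test | Week 36, z test | Week 36, visit-level df |
|---|---|---|---|---|
| Equal | AIC, all four | 5.0-5.2% | 5.1-5.4% | 4.4-4.7% |
| 1:1.1:1.2 | AIC, all four | 4.2-4.3% | 6.3-7.6% | 5.9-6.3% |
| 1:1.1:1.2 | AIC, CS or AR(1) only | 3.3-3.6% | 7.2-8.6% | 6.9-7.0% |
| 1:1.1:1.2 | Fixed unstructured | 5.2-5.3% | 5.6-6.2% | 4.9-5.5% |
| 1:1.25:1.5 | AIC, all four | 4.8-5.2% | 5.7-6.8% | 5.0-5.9% |
| 1:1.25:1.5 | AIC, CS or AR(1) only | 1.5-2.1% | 10.1-12.2% | 9.5-10.8% |
| 1:1.25:1.5 | Fixed unstructured | 5.2-5.5% | 5.4-5.8% | 4.8% |

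Visit-level df means the number of participants at the visit minus 3. Under mild growth, AR(1) was chosen in 62-64% of trials although unstructured was available. Under strong growth with 14% dropout, unstructured was chosen in 84%, which is why the larger departure does less harm.

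**4. Complete-data simulations.** These used 31 per arm and selection among compound symmetry, AR(1) and unstructured. With SDs of 44/48/53 m, BIC gave 2.9% at week 12 and 7.0% at week 36; AIC gave 3.8% and 6.0%; fixed unstructured gave 4.4% and 4.8%. A separate run with t-based tests and SDs of 44/48/53 or 40/48/56 m gave week-36 error of 5.2-5.9% (AIC) and 6.1-7.8% (BIC), week-12 error of 3.3-5.3%, and 4.4-5.8% for fixed unstructured.

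**5. Size of the week-12 loss.** In step 3, mild growth with 14% dropout and all four candidates gave a mean week-12 standard error 1.036 times the true one. The noncentrality at 31 per arm is 36/(48.2√(2/31)) = 2.94, so power falls from Φ(2.94 − 1.96) = 83.7% to about Φ(2.94 − 1.96 × 1.036) = 81.9%. This takes 48.2 m as the week-12 SD and is only a rough guide.

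**The case against.** **The size depends on assumptions.** The documents give one SD and nothing on correlations, growth in variance, candidates or criterion. With equal variances, selection did no harm. This stands: the direction is conditional and no single figure can be claimed.

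**Part of the excess is the test, not the selection.** With z tests, fixed unstructured itself reached 6.2% at week 36 under heavy attrition. This also stands. With visit-level df, AIC selection among all four under SD growth gave 5.0-6.3%, against 4.8-5.5% for fixed unstructured.

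**A reader might infer that the primary test has an inflated false-positive rate.** The documents and calculations do not support that. The distortion at week 12 runs towards conservatism, and the article does not make clear that the selected model supplies the primary p-value. Weeks 1 and 12 are the only visits in the 12-week period. A baseline-adjusted comparison at week 12 has one follow-up value per participant, so no within-participant covariance structure would have to be chosen.

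**A reader might also infer that the unstructured model is free, or that the analyst could steer the treatment effect.** It is not free; the costs are given under the fix. Comparing covariance structures by fit is common and does not target the treatment effect.

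**The article may condense a fuller plan.** An unnamed candidate list or criterion is therefore not the complaint. The comparison on trial data is stated, and naming a criterion would not cure it: every simulation used a fixed rule, AIC or BIC.

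**Conclusion.** The point holds in a limited form. The article commits to data-driven selection of the covariance structure. If spread grows over follow-up, the week-12 test becomes slightly conservative and the week-36 test slightly anti-conservative. With unstructured among the candidates, week-36 type I error is about 5-8% across the SD patterns, dropout levels and criteria tried. With compound symmetry and AR(1) alone it is about 7-12%; the article allows that pair but does not specify it. With equal variances there is no harm. These sizes rest wholly on assumed SD and correlation patterns and, where dropout was simulated, on dropout completely at random. The change is worth making because it is cheap and takes an unnecessary data-dependent step out of the follow-up tests, but no error in the primary week-12 conclusion has been shown.

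**What to change.** Replace the comparison of structures with wording such as: *The mixed model will use an unstructured within-participant covariance, fitted by REML with Kenward-Roger degrees of freedom. If it does not converge, a heterogeneous-variance structure, named here in advance, will be used. Other structures will be fitted only as sensitivity analyses.*

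**Cost.** One passage of analysis text, with the sample size unchanged at 62 (72 recruited). With k visits, unstructured has k(k+1)/2 covariance parameters: 6 for three follow-ups, or 10 if baseline is a response, against 2 for compound symmetry or AR(1). If a simpler structure is true, the lower degrees of freedom cost about one point of power (83.7% normal against 82.5% t at 31 per arm).

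**Limits of the evidence for the fix.** Kenward-Roger was not simulated; visit-level df stood in for it and kept fixed unstructured at 4.5-5.1% at week 12 and 4.8-5.5% at week 36 in all six scenarios. As a fallback, heterogeneous compound symmetry with the same df gave 4.8-5.6% at week 36 under SD growth. Robust standard errors were not tested and could be too small with about 31 per arm, so the fallback should not depend on them.

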#### Primary outcome

Consistent with the finding that people with MS report mobility limitations as their greatest concern [5], the primary outcome will be walking mobility. This will be measured by the Six Minute Walk Test (6MWT), Timed Up and Go test (TUG) and the Multiple Sclerosis Walking Scale-12 (MSWS-12) in order to capture walking endurance, walking speed and participant-reported limitations in walking.

The 6MWT will involve the participants being instructed to walk for six minutes as quickly and safely as possible [33] and the distance (m) covered will be recorded. The 6MWT has demonstrated excellent test-retest reliability and concurrent validity among people with mild to moderate MS [33].

For the TUG, the participants will be instructed to stand up from a chair, walk 3 m, then turn around walk back to the chair and sit down, as quickly and safely as possible. The participants’ performance will be timed and the mean score of three performances of the TUG will be used in analysis. TUG-cognitive involves adding a cognitive task (subtracting three from a random number between 20 and 100) while performing the TUG. Previous research demonstrates excellent test-retest reliability for people with mild MS (EDSS: 0–4) [34].

The MSWS-12 will be used to measure participants’ self-reported walking limitations due to MS during the previous two weeks. All items are measured on a likert scale ranging from 1 (not at all) to 5 (extremely). Psychometric testing of the MSWS-12 has demonstrated that it has excellent internal consistency [35,36], test-retest reliability [37] and concurrent validity [38].

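### The primary test is not fixed: three unranked walking measures, a different variable in the analysis section, and an unadjusted 0.05 for every test

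*Protocol article*

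**What the plan says.** Four parts of the protocol article bear on which test decides the trial.

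- **Primary outcome.** The section states that "the primary outcome will be walking mobility" and continues: "This will be measured by the Six Minute Walk Test (6MWT), Timed Up and Go test (TUG) and the Multiple Sclerosis Walking Scale-12 (MSWS-12"). The three instruments are meant to cover endurance, speed and self-reported limitation, and none is ranked first. The paragraph on the TUG adds that "TUG-cognitive involves adding a cognitive task", without saying whether this variant is also primary.
- **Statistical analysis.** The primary response variable is defined as "namely the difference in mean steps between the two treatment arms across the 12 week time period". The section then says: "Several analyses will be performed to compare the change in the primary response variable across time and between groups". These include mixed models with alternative covariance structures; none is named as decisive. On error control it says only: "All tests of significance will be two-sided and conducted at an alpha = 0.05 level of statistical significance".
- **Sample size.** The calculation assumes "an average improvement in 6 Minute Walk Test (6MWT) distance of 36 m", with an SD of 48.2 m, 80% power and a 5% level. It gives 31 per arm (62 in total), with 72 to be recruited. The TUG, the MSWS-12 and step count do not enter it.
- **Background.** The hypothesis is that the experimental group will "achieve significantly more improvement in walking mobility than the control group post-intervention (12 weeks) and that this improvement will be maintained" at weeks 24 and 36.

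As an outcome, step count appears only under Secondary outcomes, from the armband and the exercise logs.

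**The concern.** A confirmatory trial needs one pre-stated answer to the question of which result counts as success. Here the Primary outcome section offers three variables, the Statistical analysis section a different one, and the Sample size section a single one of the three. With each test at the full 0.05 and no success rule, nothing prevents a significant result on whichever walking measure does best from being reported as an effect on walking mobility. That would raise the type I error of the primary claim above 5%. If the measures disagree, for example a gain on the MSWS-12 but none on the 6MWT, the plan does not say what the trial has shown.

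**Working it through.** **Inputs.** From Sample size: difference 36 m, SD 48.2 m, two-sided 5%, 80% power, 31 per arm, 72 recruited. From Primary outcome: three listed measures, with TUG-cognitive as a possible fourth. From Statistical analysis: every test at 0.05. The documents give no correlation between measures, so a range from 0 to 0.9 is assumed.

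**1. The plan's own figure.** The standardised difference is 36/48.2 = 0.747. The normal approximation gives n per arm = 2(1.960 + 0.842)²/0.747² = 28.1, so 29. With the noncentral t, 30 per arm gives 81.2% power and 31 per arm gives 82.5%. The stated 31 per arm is therefore reproduced to within one per arm. It is the size for one endpoint, the 6MWT, at the full 0.05.

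**2. Error if any one measure suffices.** For k independent tests the chance of at least one false positive is 1 − 0.95^k:

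- k = 3: 1 − 0.8574 = 14.3%
- k = 4: 1 − 0.8145 = 18.5%

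For test statistics with common correlation ρ and c = 1.96, it is 1 − ∫ φ(x) [Φ((c − √ρ x)/√(1−ρ)) − Φ((−c − √ρ x)/√(1−ρ))]^k dx. Numerical integration gives:

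| Assumed correlation | 3 measures | 4 measures (with TUG-cognitive) |
|---|---|---|
| 0 | 14.3% | 18.5% |
| 0.5 | 12.5% | 15.6% |
| 0.7 | 10.9% | 13.0% |
| 0.9 | 8.4% | 9.4% |

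**3. Error if all three must succeed.** The chance that all are significant cannot exceed the chance that any given one is, so the error is at most 5%. The cost is power. The documents give no effect size for the TUG or the MSWS-12, so joint power cannot be derived from them. As an illustration, if each had the 6MWT's 82.5% and they were independent, it would be 0.825³ = 56%. It would be higher with positive correlation, but never above 82.5%.

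**4. Error if the 6MWT alone decides.** It is 5%, and 31 per arm stands.

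**5. Cost of splitting alpha three ways.** At 0.05/3 = 0.0167, power for the 6MWT at 31 per arm falls from 82.5% to 68.3%. Restoring 80% needs 39 per arm, or 78 evaluable. That already exceeds the 72 to be recruited. At the implied dropout of 1 − 62/72 = 13.9%, recruitment would have to be 78 × 72/62 = 90.6, so 91.

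**The case against.** The strongest reply is that the plan never says any one measure suffices. The Statistical analysis section speaks of one primary analysis of one variable, and the Sample size section uses one measure, which suggests a single lead endpoint. Testing everything at two-sided 0.05 is also compatible with a fixed-order procedure or an all-must-succeed rule. This is a condensed article, and a hierarchy is commonly left to a statistical analysis plan.

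Much of this stands. The error figures are conditional, and the lack of a written hierarchy alone would not be a finding. The reply does not rescue the plan, however. The one variable named in the analysis section is mean steps, which is neither the variable used for sizing nor any of the three listed as primary. The sections conflict in what they state, and an analysis plan could settle this only by departing from at least one of them.

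Three stronger readings are tempting but unsupported.

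- A reader might infer that the false-positive rate simply is 11 to 18%. That requires an any-one-suffices rule that is not stated. The lower end is just the value at an assumed correlation of 0.7, and the upper end counts TUG-cognitive, which is outside the list of three.
- A reader might multiply three measures by three follow-ups into nine chances of success. The hypothesis asks for improvement at week 12 and its maintenance afterwards, and the primary analysis is tied to 12 weeks. The later visits are added requirements, not alternative routes to success.
- A reader might add inflation for the several planned analyses. Their number is not given, and comparing covariance structures is ordinary mixed-model practice that need not involve choosing on the treatment effect. No figure can be attached to it.

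**Conclusion.** The concern holds in a conditional form. The article does not fix a single primary test: the Primary outcome, Statistical analysis and Sample size sections give three different answers, and every test is allowed the full 0.05. If success on any one of the three listed measures counts, the error is about 8 to 14% for assumed correlations from 0.9 down to 0. It could be as high as 18.5% only if TUG-cognitive is treated as primary too. Under an all-must-succeed rule it is at most 5%, and with the 6MWT alone it is 5%. The document does not say which case applies, so no single error rate can be attributed to the plan. This should be settled before the data are analysed, because it decides what the trial may claim. The contradiction is certain from the text; the size of the inflation depends on the assumed rule and correlations.

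**What to change.** - Name baseline-adjusted 6MWT distance at week 12 as the single primary test at two-sided 0.05. This matches the sample size and the 12-week period in the analysis section.
- In Statistical analysis, replace mean steps with 6MWT distance as the primary response variable, and keep step count among the secondary outcomes.
- Make the TUG, TUG-cognitive, the MSWS-12 and all week 24 and 36 contrasts secondary, or test them in a stated fixed order after the 6MWT.
- Name one mixed model as primary before unblinding and label the other analyses as sensitivity analyses. The choice of covariance structure and degrees-of-freedom method can be left to the analysis plan.

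The cost is protocol wording, and 62 evaluable participants remain sufficient. The downside is that the TUG and the MSWS-12 lose their equal primary standing. Keeping all three with a three-way alpha split would preserve it, but at the loss of power shown above or with a larger trial.

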A recent multi-centre block randomised controlled trial, which evaluated the effectiveness of community exercise interventions for people with MS who had minimal gait impairment, demonstrated significant benefits of exercise in the community [20]. Physiotherapist- and fitness- instructor- led interventions consisted of combined aerobic and strengthening training components. That exercise intervention resulted in significant improvements in the physical impact of MS, psychological impact of MS, impact of fatigue and walking endurance [20]. Of note, however, is that these improvements were not maintained over the longer term and the effect on the primary outcome measure (walking mobility) was no longer significant 12 weeks post-treatment [20]. Moreover, there was significant attrition with 50% loss to follow up at 24 weeks [20]. It is therefore imperative that future research interventions facilitate long-term adherence and positive changes in PA behaviour, in order to inform the implementation of sustainable exercise interventions for people with MS.

A behavioural outcome of paramount importance for optimised, long-term effectiveness of exercise programmes is exercise-adherence, particularly post-intervention PA behaviour [21].

Social Cognitive Theory (SCT) is one of the most widely-adopted theoretical frameworks for understanding and optimising PA and other health behaviours. Along these lines, researchers have developed a programme of work investigating a SCT-based behaviour change intervention. The intervention involves workshops that aim to enhance exercise self-efficacy and focus on the provision of information relative to PA participation based on the principles of SCT; namely outcome expectations, self-efficacy, impediments and goal setting. Previous research has demonstrated that individuals who completed the SCT-based intervention attended more exercise sessions than individuals in the standard care group [22]. Subsequent research using an online delivery [23] observed significant positive effects on PA as measured by the Godin Leisure Time Exercise Questionnaire that were subsequently replicated as a significant, large increase on accelerometer step counts [24]. Supplementing the programme with video coaching further increased PA and this change was maintained 12 weeks post-intervention [25].

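### The planned multiple imputation assumes missing at random, so it cannot show what happens to the conclusion if data are missing not at random

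*Protocol article*

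**What the plan says.** Four elements of the Statistical analysis section bear on this point.

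- **Main modelling.** Several analyses of change over time are planned: "These will include linear mixed models for a continuous response with different covariance structures compared". Mixed models are part of that set. The section does not say that they are the whole of the primary analysis.
- **Purpose of the imputation.** A further comparison of the estimated effect is made "when imputing values for all missing data in order to investigate the assumptions relating to missingness", together with any effect on the overall conclusion.
- **Method of the imputation.** "Multiple imputation will be performed using a Predictive Model Based Method using chained equations where each missing value is replaced by 20 imputed values". Estimates from the completed data sets "will be averaged using the Barnard-Rubin adjustment method". No shift of imputed values, pattern-mixture model or reference-based rule is mentioned.
- **Descriptive work.** The level of missing data is reported, reasons for dropout are recorded where possible, and "an analysis into the cause of missingness (if present) will be conducted".

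The Background says of the earlier community exercise trial that "there was significant attrition with 50% loss to follow up at 24 weeks". The hypothesis at the end of the Background includes maintenance of the benefit at weeks 24 and 36.

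**The concern.** A sensitivity analysis tests an assumption only if it relaxes that assumption. A likelihood-based mixed model is valid when missingness depends only on observed data. Chained equations draw each missing value from a model fitted to observed data, which is the same kind of assumption. Setting one beside the other therefore leaves out the departure that cannot be checked from the data: people with missing values who do worse, or better, than their observed data predict.

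That departure is plausible here. The trial concerns adherence, and people who stop exercising may also be the ones who miss assessments. Only one arm receives content aimed at sustaining exercise, so the pattern could differ by arm. If the mixed model and the imputation agree, the agreement could be taken as support for the conclusion on a point that neither analysis has examined.

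**Working it through.** **Inputs**

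| Input | Value | Source |
|---|---|---|
| Planning effect and SD, 6MWT | 36 m, 48.2 m | Sample size: "improvement in 6 Minute Walk Test (6MWT) distance of 36 m with an estimated standard deviation of 48.2 m" |
| Needed / recruited | 62 / 72 | Sample size |
| Imputations and pooling | 20, Barnard-Rubin | Statistical analysis |
| Loss at 24 weeks, earlier trial | 50% | Background |
| Departure from MAR | 20 m, SCT arm only | **Assumption**, not in the documents |

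**The plan's own figure.** The normal approximation gives n per arm = 2 × (1.960 + 0.842)² × 48.2² / 36² = 28.1, so 29 per arm. The noncentral t gives 30 per arm (power 81.2%). At the stated 31 per arm, power is 82.5%. The figure of 62 is therefore reproduced to within 2 participants. The present point does not depend on it.

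**Implied dropout.** 1 − 62/72 = 13.9%. The article states no rate.

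**What each planned step assumes**

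| Step | Missingness assumption | Can it show sensitivity to MNAR? |
|---|---|---|
| Linear mixed model | MAR given the model's variables | No |
| Chained-equation imputation as described | MAR given the imputation variables | No |
| Analysis of causes of missingness | Descriptive | No; it sees only recorded data |

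**Size of a shared bias.** Let p be the proportion missing in the SCT arm and d the amount by which those participants fall short of the MAR prediction. The difference for all randomised participants is then the MAR estimate minus p × d, so bias = p × d.

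| d (assumed) | p = 13.9% | p = 50% |
|---|---|---|
| 10 m | 1.4 m | 5 m |
| 20 m | 2.8 m (8% of 36 m) | 10 m (28% of 36 m) |
| 40 m | 5.6 m | 20 m |

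If the same shortfall applies in both arms, the bias is d × (p in SCT arm − p in control arm). It vanishes when loss is equal.

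**Does the comparison reveal it?** Two simulations used 36 per arm, one follow-up, SD 48.2 m, a baseline-adjusted observed-data model, and imputation with 20 sets from the same variables.

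1. *Fixed departure* (1,500 trials): 50% missing, SCT-arm dropouts 20 m worse than MAR predicts, true difference −10 m. The observed-data model averaged −0.23 m and imputation −0.15 m, with correlation 0.97.
2. *Dropout driven by the unobserved outcome* (1,000 trials per setting). Assumptions: SCT arm only, log-odds slope −1 per SD, baseline SD 90 m, missing rates averaged over both arms.

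| Missing | True | Observed-data model | Imputation | Rejection rate (5% nominal) |
|---|---|---|---|---|
| 14% | 0 m | 6.6 m | 6.6 m | 8.3%, 7.7% |
| 14% | 36 m | 43.4 m | 43.4 m | – |
| 50% | 0 m | 19.1 m | 19.2 m | 23.3%, 20.7% |
| 50% | 36 m | 55.7 m | 55.7 m | – |

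The two estimates correlate at 0.99 to 1.00. With the same variables in both models, they agree while both are wrong.

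**What the comparison can reveal.** In a third simulation (1,000 trials per setting, true difference 36 m), SCT-arm dropout depended on recorded adherence (assumed correlation with outcome 0.5), and adherence entered the imputation model only. At about 50% missing, the observed-data model gave 46.1 m and imputation 36.0 m. At about 14%, the figures were 40.1 m and 36.2 m. Across correlations of 0.3 to 0.7, the gap was about 2 to 14 m. The comparison thus detects a poor choice of conditioning variables. Here the data are MAR given adherence, so the result says nothing about MNAR.

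**The case against.** The strongest reply has four parts.

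- **The assumptions need not be identical.** Mixed models are only among several analyses. If the 12-week comparison used completers only, imputation beside it would be informative. The imputation variables are not listed, and the trial records attendance, walking duration and step counts. A reader might infer that the two analyses must share the same bias and agree. The documents do not support that, and the third simulation shows they can differ. This part stands.
- **The text never mentions MNAR.** It speaks of missingness assumptions in general and does not say that agreement will be read as robustness. This is correct. However, the stated aim covers those assumptions and the effect on the conclusion, and the named method leaves the main one untouched.
- **The magnitude is an assumption.** A reader might infer that the bias is 10 m, or 28% of the planning effect. That figure is an assumed 20 m multiplied by another trial's 24-week loss. At the dropout this plan allows for, the same assumption gives 2.8 m. This part stands too.
- **The details belong in an analysis plan, and causes of missingness will be studied.** A delta grid can indeed sit in an analysis plan, which is not shown. But the article itself fixes purpose, method, number of imputations and pooling, so the mismatch is in what it states. The descriptive work is useful but cannot rule out MNAR.

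A reader might also infer that 20 imputations are too few. That has no bearing on this point, and nothing in the documents shows it to be an error.

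**Conclusion.** The concern holds in a limited form. The imputation is given a purpose that the named method serves only in part: it can examine the conditioning set or a completers-only analysis, but not departures from MAR. None of the objections changes that.

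The size in this trial is unknown. Under an illustrative 20 m one-arm departure it is about 2.8 m at 14% missing and 10 m at 50%. The 20 m, its restriction to one arm and the simulated dropout mechanisms are assumptions, and the 50% comes from a different trial. The concern is smaller for the 12-week comparison and greatest for weeks 24 and 36, where loss is likely to be higher and the maintenance claim rests. The conclusion that MAR is assumed follows from the methods named, since the article does not use the term. This is a correctable mismatch that should be put right, not a fault that invalidates the analysis.

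**What to change.** 1. Describe the chained-equation imputation as an analysis under missing at random, and limit its stated purpose accordingly.
2. Add a pre-specified delta-adjusted (tipping-point) analysis of 6MWT on the same imputed sets. Shift the imputed values by fixed amounts, for example 0 to −40 m in 10 m steps, first in the SCT arm and then in both arms. Re-pool each time and report the shift at which the conclusion changes. Cover weeks 24 and 36 as well as week 12.
3. Optionally, add a control-arm reference-based imputation.

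If no such analysis is wanted, the alternative is to remove the claim that the imputation investigates the missingness assumptions. The cost is a few lines of code and a change of wording, with no new data, best settled before unblinding. The downside is a little extra analysis and possibly a less favourable statement about robustness.
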